### Contamination

Participants will be able to use any co-intervention they wish. Since it is likely that other (vocational) rehabilitation programs will have a significant effect on return to work, participation in one of these co-interventions will be monitored by means of follow-up questionnaires.

In theory, participants could provide knowledge about the intervention and even access to Cancer@Work to participants in the control group. However, as participants will be recruited individually via outpatient clinics of hospitals and not, for instance, via support groups, the chance that a patient from the intervention group will know a patient from the control group is nil. Nonetheless, we will ask participants in the control arm, via follow-up questionnaires, whether they received any support related to return to work.

### Usual care in the Netherlands

Currently work-related issues are not structurally addressed as part of cancer (survivorship) care in the Netherlands. However, it is becoming more common to discuss this issue with a care provider at the hospital or to receive support by a reintegration office specialised in patients with cancer.

All sick-listed employees should have an occupational physician who should legally advise them about return to work according to the blueprint of evidence-based guidelines of the Dutch Association of Occupational Physicians [31]. The Improved Gatekeepers Act covers sick leave in the Netherlands and is in force during the first 2 years of sick leave. The act states that a sick-listed employee cannot be discharged and receives at least 70 % of his/her wage. The Improved Gatekeepers Act states that employers and sick-listed employees are together responsible for work resumption, which means that both parties can be sanctioned.

In the Netherlands, the social security system also provides a safety net for sick-listed workers without an employment contract according to the Improved Gatekeepers Act. Application of the Act is the same, except that these workers do not have an employer/workplace to return to. Sick-listed workers without an employment contract receive 70 % of their last daily wage during the first 2 years of sick leave. The Dutch Social Security Agency pays for the sick leave, is responsible for executing obligatory occupational health actions and should facilitate work resumption.

Self-employed persons can be privately insured against sickness absence, but most are uninsured because of the high costs. If a person is privately insured, it depends on the insurance policy as to when someone receives a supportive income, how much this supportive income is and whether or not he/she receives sickness absence counselling and vocational rehabilitation guidance.

### Training specialised nurses to carry out the Cancer@Work intervention

Specialised nurses will be educated on the work-related issues of cancer patients, the social security system of the Netherlands, how to coach patients with self-management based on problem-solving techniques, how to deliver personalised feedback and how to encourage patients to comply with the Cancer@Work intervention [32]. Training of the specialised nurses will consist of two half-day training courses, supervised by an experienced trainer and a member of the research team.

### Assessment of the outcomes

Data will be both self-reported and collected by recording use of the Cancer@Work intervention by participants and recording the content of the assignments made by participants. The self-reported outcomes will be assessed at baseline and at 3, 6, 9 and 12 months of follow-up using questionnaires that will be completed by participants randomised to the intervention group and control group with online software. All participants will receive an email with a link to complete the questionnaire online if they indicate to prefer questionnaires online; otherwise, they will receive paper questionnaires. Completing a questionnaire will take approximately 30 minutes.

#### Feasibility evaluation

The following feasibility outcomes will be measured according to the Bowen scheme [33]: acceptability, demand, practicality and compliance with the Cancer@Work intervention. By acceptability we mean general usefulness of the Cancer@Work intervention and of each functionality, general user-friendliness of the Cancer@Work intervention and of each functionality, appropriateness of the intervention for the patient, satisfaction with support of their specialised nurse in their use of the Cancer@Work intervention, information that should be useful to add to the Cancer@Work intervention, functionalities that should be useful to add to the Cancer@Work intervention and general ideas to improve the Cancer@Work intervention. All these parameters will be measured at the patient level with self-reported questionnaires at follow-up.

We define demand as the extent to which the Cancer@Work intervention has actually been used and include number of log-ins into the Cancer@Work intervention, use of each functionality of the Cancer@Work intervention (number) and the number and the content of assignments. These will all be measured based on a website monitoring program. To assess practicality we will evaluate the self-perceived knowledge and skills of the specialised nurse regarding the intervention, protocol for the specialised nurse, website for the specialised nurse and appropriateness of the training and preparation of the specialised nurse. These will all be assessed as part of the semi-structured interview with the specialised nurse at the end of the study.

Compliance by patients will be measured with a website monitoring program. Reasons for non-compliance will be measured based on self-reported questionnaires at follow-up as well as on whether or not use of the Cancer@Work intervention fits in the patient’s daily routine, since that is often a reason for not complying.

#### Effect evaluation

The primary outcome of sustainable return to work is measured as any return to work (yes/no) at follow-up independent to the number of contract hours which is sustained for at least 4 consecutive weeks without recurrent sick leave. Return to work is either partial return to work (working a part of contract hours) or full return to work (working all contract hours).

The secondary outcomes are full return to work (yes/no) at follow-up defined as working the hours stated in the work contract, time to any (either partial or full) return to work in days from the first day of sick leave to the date of any return to work and time to return to work in days from the first day of sick leave to the date of full return to work. These return-to-work measures must be sustained for at least 4 consecutive weeks. Furthermore, secondary outcome measures are work ability using the first three questions of the Work Ability Index (WAI) [34], work functioning using the Work Limitations Questionnaire (WLQ) [35, 36], quality of life using the SF-12 [37], quality of work life using the QWLQ-CS (De Jong et al. in preparation) [38] and the time from initial sick leave to full return to work without extensive need for recovery using a subscale of the ‘perception and assessment of work questionnaire’ (VBBA) [39].

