### Participants

Eligible for this study will be patients with a primary diagnosis of cancer who will be treated with curative intent at the hospital of recruitment, between 18–62 years old, in paid employment or self-employed and who have sufficient knowledge of the Dutch language. Patients will be excluded if they have a severe comorbidity or if they have no Internet access.

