### Sample size

On average, we will include cancer patients at 6 weeks or 42 days after diagnosis, and the follow-up time for the primary outcome return to work will be 12 months after inclusion, hence 12 months and 42 days after diagnosis. Earlier studies in our hospital showed that return to work for patients with various cancer types was 64 % at 12 months of follow-up from diagnosis [28]. In addition, earlier studies in our hospital showed that return to work in the first 42 days is around 8 % [28]. Therefore, the return to work for the control group was set at 64 % + 8 % = 72 %. In a study of Nieuwenhuijsen et al. [29], an intervention group of 35 radiotherapy patients received a supportive work-related intervention in a hospital. Time between diagnosis and the end of treatment was a median 42 days. Return to work was measured between the end of treatment and work resumption and was 89 % after 12 months. Therefore, the return to work for the intervention group in our intervention was also set at 89 %.

Based on our earlier studies on consecutive cancer patients, a power analysis indicated that we should include a total of 170 patients with a follow-up of 1 year after inclusion to indicate a difference of 89 % return to work in the intervention group versus a 72 % return-to-work rate in the control group, with a power of 80 % and *p* < 0.05. Accounting for 10 % loss to follow-up, 190 patients should be included.

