#### Economic evaluation

The economic evaluation will be conducted from a societal perspective. The following direct costs will be measured for both groups: costs to deliver the Cancer@Work intervention or costs to deliver care as usual and the following indirect costs: absenteeism, lost work productivity, lost earnings and work adjustments. The direct costs will be determined by means of the costs to deliver the Cancer@Work intervention (i.e. costs to develop and maintain the e-health intervention, average specialised nurse wage, the amount of time spent on each participant and training costs) or costs to deliver care as usual (i.e. average specialised nurse wage and the amount of time spent on addressing return to work of each participant). Absenteeism costs will be determined by means of total days on sick leave from the first day of sick leave until follow-up and on income and work productivity costs by the WLQ and on income [35, 36]. Additionally, lost earnings will be determined on the basis of the differences between income at baseline and income at follow-up. Work adjustments will be assessed by means of the cost of each work adjustment.

Direct costs will be acquired by the specialised nurses keeping track of the time spent on each participant and by the research team on keeping track of the costs to develop and maintain the Cancer@Work intervention and training costs to train specialised nurses to deliver the Cancer@Work intervention. Indirect costs will be acquired by a self-reported questionnaire completed by participants during follow-up.

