#### Effectiveness secondary parameters

The number of days until participants’ return to work (either full or partial) assessed at 12 months will be analysed using the Kaplan-Meier survival method, and differences between groups will be tested with the log-rank test. Patients who dropped out of the study will be censored. If statistically significant differences in prognostic characteristics between the intervention and the control group are found at baseline, a Cox regression analysis will be performed including those prognostic parameters.

A longitudinal multilevel analysis will be used to examine differences between intervention and the control group with regard to improvement of work ability, work limitations, quality of work life and quality of life.

A cut-off score of ≥6 on the subscale need for recovery of the VBBA will be used to divide the group of participants who returned to work without extensive need for recovery versus the group of participants who returned to work with an extensive need for recovery plus the participants who did not return to work. The number of days until participants’ return to work without extensive need for recovery at 12 months will be analysed using the Kaplan-Meier survival method, and differences between groups will be tested with the log-rank test. If statistically significant differences in prognostic characteristics between the intervention and the control group are found at baseline, a Cox regression analysis will be performed including those prognostic parameters.

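### The three secondary time-to-return outcomes start at the first day of sick leave, before randomisation, with no delayed entry: curves and medians include untreated days, and some log-rank power may be lost

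*Protocol article*

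**What the plan says.** **Time origin.** The Effect evaluation section of the protocol article lists three time-to-return outcomes, all secondary:
- any return: "time to any (either partial or full) return to work in days from the first day of sick leave to the date of any return";
- full return: "time to return to work in days from the first day of sick leave to the date of full return to work";
- the need-for-recovery outcome: "the time from initial sick leave to full return to work without extensive need for recovery".

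Partial resumption counts as a return, and a return must last four weeks.

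**Analysis.** Under Effectiveness secondary parameters, days to return "will be analysed using the Kaplan-Meier survival method, and differences between groups will be tested with the log-rank test". The need-for-recovery outcome is treated in the same way. No entry at randomisation is mentioned.

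**Timing of entry.** Recruitment takes place some weeks after initial treatment, and randomisation follows consent. The Sample size section says: "On average, we will include cancer patients at 6 weeks or 42 days after diagnosis". It adds, from earlier studies at the hospital, that "return to work in the first 42 days is around" 8 %.

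**Who can enter.** The Abstract limits eligibility to patients who are on sick leave. The Participants section asks for patients "in paid employment or self-employed and who have sufficient knowledge of the Dutch language" and lists no sick-leave condition.

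**Costs.** Under Economic evaluation, absenteeism is based on "total days on sick leave from the first day of sick leave until follow-up".

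**The concern.** Randomisation makes the arms comparable from the moment of allocation. A clock that starts earlier brings two things into the comparison that allocation cannot influence.

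1. **Event-free time.** A patient who is randomised while still off work cannot have had the event before entry. Plain Kaplan-Meier from the first sick day nevertheless counts that patient as at risk throughout that time. The resulting median is not time under allocated care. It is also too long as an estimate of time from first sick leave, because patients who returned early never entered.
2. **Events before allocation.** If patients already back at work, even partly, can be randomised, their returns count as events that carry no information about treatment. They pull the hazard ratio towards 1.

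At stake are the secondary return-to-work durations, which readers are likely to quote, and the precision of the absenteeism cost difference.

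**Working it through.** **Plan's own figure.** With 72 % versus 89 %, two-sided 0.05, 80 % power, pooled variance and no continuity correction, the result is 85 per arm, or 170 in total, as stated (power at 85 per arm: 80.4 %). This rests on the yes/no primary outcome, so the clock does not enter it.

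**Inputs.** From the document: 72 % and 89 % at 12 months, 85 per arm, mean 42 days from diagnosis to inclusion, and the historical 8 %. Assumed: exponential return times after randomisation, no dropout, the distribution of the lag from first sick day to randomisation (the document gives only a mean, and from diagnosis), and 8 % as the share already back at entry.

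**Implied hazard ratio.** ln(0.11)/ln(0.28) = 1.73.

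**Control median.**
- Rate: -ln(0.28)/365 = 0.003488 per day.
- From randomisation: ln 2/0.003488 = 199 days.
- From first sick day, constant 42-day lag, nobody back at entry: 199 + 42 = 241 days. With a variable lag of the same mean, simulation gives up to about 245.
- If 8 % are already back, constant lag: 42 + ln(0.92/0.50)/0.003488 = about 217 days. Here event-free time and early events offset each other in part.

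**Log-rank power.** Simulated, 85 per arm, hazard ratio 1.73, 1,500 trials per row. Each cell shows the clock from randomisation, then the clock from first sick day.

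| Assumed lag (days) | Nobody back at entry | 8 % already back |
|---|---|---|
| constant 42 | 88.7 % / 88.7 % | 86.9 % / 84.1 % |
| uniform 14-70 | 91.1 % / 90.8 % | 86.9 % / 82.2 % |
| lognormal, mean 42, log-SD 0.6 | 89.7 % / 89.0 % | 87.7 % / 83.7 % |
| uniform 0-180 | 89.3 % / 87.8 % | 88.4 % / 81.9 % |
| lognormal, mean 90, log-SD 0.8 | 89.7 % / 84.1 % | 87.3 % / 79.3 % |

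A second set used gamma lags with mean 42 and SD 20-60 days. It gave losses of 1-3 points with nobody back, and 4-7 points with 8 % back. For a weaker true hazard ratio of 1.50 with 8 % back, power fell from 62 % to 53-57 % and the estimate was 1.43-1.45.

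**Hand check of the 8 % case, constant lag.**
- Events before randomisation: 0.08 × 170 = 13.6.
- Events after: 0.92 × 85 × (0.72 + 0.89) = 125.9.
- Share carrying no treatment effect: 13.6/139.5 = 9.7 %.
- Approximate estimate: exp(0.903 × ln 1.734) = 1.64, in line with the simulated 1.63-1.66. A widely spread lag lowers it a little further.
- Power, using z = ln(HR) × √events/2 - 1.96: from randomisation 0.550 × √125.9/2 - 1.96 = 1.13, or 87 %; from first sick day 0.497 × √139.5/2 - 1.96 = 0.97, or about 83 %.

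**Delayed entry.** Keeping the sick-leave clock but entering patients at randomisation gave power within about 1 point of the randomisation clock in every row.

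**Type I error.** With no true effect, rejection was 5.6 % in 2,000 trials on the sick-leave clock and 4.7 % from randomisation. The simulation SE is √(0.05 × 0.95/2000) = 0.5 points, so both agree with 5 %.

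**Absenteeism.** If sick days before randomisation have an SD of 20-60 (assumed), the chance difference between arms of 85 has an SE of SD × √(2/85), about 3-9 days. Its expectation is zero.

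**The case against.** The strongest reply is that the harm to the test depends on patients already back at work being randomised. The Abstract requires sick leave, which would largely exclude them. The 8 % is a historical rate used to extend the control rate from 64 % to 72 %; nowhere does the plan say that 8 % of enrolled patients will have returned. Applying it on top of 72 % gives a control return of 0.08 + 0.92 × 0.72 = 74 %, which is not the plan's figure. The lag from first sick day is not given either, and the roughly 6-point loss with nobody back needs a skewed lag averaging 90 days, which the document does not suggest. All of this stands, and it is why the power loss is stated as conditional.

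It can also be said that duration from first sick leave is meaningful in its own right, and that delayed entry is a detail an unseen analysis plan could supply. The first part is fair and argues for keeping that duration as a description. The second stands only in part: the time origin and the log-rank test are fixed in the article, and the origin precedes randomisation.

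A reader might infer that time before randomisation by itself dilutes the comparison. It hardly does: a lag common to all patients only shifts the axis, and only its spread matters. A reader might also infer bias towards one arm. The arms share the same distribution of lag and early returns, and the type I error stays near 5 %.

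**Conclusion.** The point holds, confined to the three secondary time-to-return outcomes and the absenteeism costs.

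- **Curves and medians.** Under either eligibility reading they mix days before randomisation with days under allocated care. With a mean lag of 42 days and nobody back at entry, the control median is about 241-245 instead of 199 days.
- **Test.** About 0-3 points of log-rank power are lost if nobody has returned at entry and the lag averages 42 days. About 4-9 points are lost (just under 3 with a constant lag) if about 8 % have returned, with 1.73 estimated as about 1.63-1.66. Early returns do most of the harm.
- **Not affected by the clock.** The primary relative risk, the 170/190 sample size and the type I error. The mean absenteeism difference is noisier but not biased.

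The second scenario can be neither confirmed nor ruled out, because the Abstract and the Participants section disagree on sick leave at entry. Even with that requirement, a patient still sick-listed but working part of the contract hours would already count as having made any return. The sizes rest on the assumptions listed with the calculations.

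**What to change.** 1. Count all three time-to-return outcomes from randomisation. Alternatively, keep the sick-leave clock and let each patient enter the risk set at randomisation.
2. Leave patients already in sustained return at randomisation out of the risk set for that outcome. Someone in partial return stays at risk for full return. State, using only information available at randomisation, how a return that has begun but not yet lasted four weeks is handled.
3. Reconcile the Abstract and the Participants section on whether sick leave is required at entry.
4. In the cost comparison, count absenteeism days from randomisation, which removes chance imbalance from the earlier period.

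The cost is a change of wording. The first sick day is already needed for the planned outcomes, and the date of randomisation should be on record from the computerised allocation. The small downside is that durations become less directly comparable with studies counting from the first sick day; that version can be reported descriptively.

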#### Prognostic and descriptive characteristics

Prognostic characteristics are age, gender, marital status (married, single, widowed, divorced), bread winner status (yes, no, shared), education (7 categories), cancer diagnosis, treatment type (surgery, radiotherapy, chemotherapy, hormonal therapy, other), time since diagnosis (in months), treatment duration and comorbidity (13 diseases). Work-related factors include characteristics of the job (working hours per week, job position, company size, shift work (no, yes with/without night shifts), type of contract (permanent, temporary, self-employed), years in present position, years of work experience, and work adjustments), work demands (VBBA) [39], importance of work (0 (not important)–100 (most important)), current problems with work (yes/no), need for information or support regarding work-related problems (1 (no)–5 (very much)) and expectations regarding return to work in next 4 weeks (1 (definitely yes)–4 (probably not)). Fatigue is measured with the 20-item Multidimensional Fatigue Inventory (MFI) [40] with higher scores indicating more fatigue, depression is measured with the 20-item CES-D [41] with higher scores indicating more depressive symptoms and cognitive functioning at work is measured with the 20-item Cognitive Symptom Checklist-Work questionnaire [42]. The following descriptive characteristics will be measured: income (in euros per month) and work participation status at follow-up (employed, unemployed, disability pension, retired).

#### Economic evaluation

The economic evaluation will be conducted from a societal perspective. The following direct costs will be measured for both groups: costs to deliver the Cancer@Work intervention or costs to deliver care as usual and the following indirect costs: absenteeism, lost work productivity, lost earnings and work adjustments. The direct costs will be determined by means of the costs to deliver the Cancer@Work intervention (i.e. costs to develop and maintain the e-health intervention, average specialised nurse wage, the amount of time spent on each participant and training costs) or costs to deliver care as usual (i.e. average specialised nurse wage and the amount of time spent on addressing return to work of each participant). Absenteeism costs will be determined by means of total days on sick leave from the first day of sick leave until follow-up and on income and work productivity costs by the WLQ and on income [35, 36]. Additionally, lost earnings will be determined on the basis of the differences between income at baseline and income at follow-up. Work adjustments will be assessed by means of the cost of each work adjustment.

Direct costs will be acquired by the specialised nurses keeping track of the time spent on each participant and by the research team on keeping track of the costs to develop and maintain the Cancer@Work intervention and training costs to train specialised nurses to deliver the Cancer@Work intervention. Indirect costs will be acquired by a self-reported questionnaire completed by participants during follow-up.

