#### Economic evaluation

Direct and indirect costs will be summed for each participant. Using bootstrapping, mean differences in direct, indirect and total costs will be calculated between the control group and the intervention group [45]. Incremental cost-effectiveness ratios will be calculated by assessing the ratio between the differences in costs between the intervention and control group to the differences in return-to-work rates between the groups.

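### The societal cost total can count part of the same sick-leave loss twice, and it omits the rehabilitation co-interventions that the trial records

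*Protocol article*

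**What the plan says.** The relevant text is in the two sections of the protocol article headed Economic evaluation, one under Assessment of the outcomes and one under Statistical analysis.

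- Perspective: "The economic evaluation will be conducted from a societal perspective".
- Indirect costs: "the following indirect costs: absenteeism, lost work productivity, lost earnings and work adjustments".
- Absence: "Absenteeism costs will be determined by means of total days on sick leave from the first day of sick leave until follow-up and on income".
- Earnings: "Additionally, lost earnings will be determined on the basis of the differences between income at baseline and income at follow-up".
- Total: "Direct and indirect costs will be summed for each participant".
- Cost-effectiveness ratio: "the ratio between the differences in costs between the intervention and control group to the differences in return-to-work rates between the groups".

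Direct costs are given as a closed list. For the intervention arm it covers development and maintenance of the e-health tool, nurse wage and time, and training. For usual care it covers nurse wage and time only.

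Two other sections bear on this. Usual care in the Netherlands says that sick-listed employees keep no less than 70% of their wage, that workers without a contract get 70% of their last daily wage, and that most self-employed people have no insurance for sickness absence. Contamination allows any co-intervention, expects vocational rehabilitation to affect return to work significantly, and states that "participation in one of these co-interventions will be monitored by means of follow-up questionnaires".

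**The concern.** A societal total should count each lost unit of work once, whoever bears the loss. If absent days are valued at the patient's usual income, the whole loss is already in the total. A drop in the patient's pay during that absence only shows how the loss is split between patient and payer. Adding the drop on top counts the patient's share again.

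The duplicate does not cancel between arms when return to work differs, because the arm with more absence carries more of it. The error then passes into the cost difference, which is the numerator of the ratio.

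The second issue is one of scope. Co-interventions may change the return-to-work rate, which is the denominator, while their cost never reaches the numerator. Cost-effectiveness is part of the second objective in the Objective section, so the definition of the total matters.

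**Working it through.** **The plan's own figure.** The economic sections state no number. The rates used below, 89% and 72%, come from Sample size. With two-sided alpha 0.05, 80% power, pooled variance and 1:1 allocation, n per arm = [1.960 × √(2 × 0.805 × 0.195) + 0.842 × √(0.72 × 0.28 + 0.89 × 0.11)]² / 0.17² = 84.1, rounded up to 85, so 170 in total as stated. Dividing by 0.90 gives 189, against 190 stated. The costing point does not depend on this.

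**Overlap per month of absence.** Set usual monthly income to 1 and let s be the share still paid while sick.

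- Absence valued at usual income: 1
- Lost earnings during that absence, if fully captured: 1 - s
- Sum: 2 - s

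| Share paid, s | Source | Costed | Counted once |
|---|---|---|---|
| 1.00 | full pay, allowed by the 70% minimum | 1.00 | 1.00 |
| 0.70 | minimum for employees; rate without a contract | 1.30 | 1.00 |
| 0.00 | assumption for uninsured self-employed | 2.00 | 1.00 |

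If absence were instead valued at the reduced income actually received, the sum would be s + (1 - s) = 1.00 with no duplication. The article does not say which income applies.

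**Does it cancel between arms?** Illustration only. Assume income of EUR 3,000 per month, 6 months' absence in those who return, 12 months in those who do not, and an intervention cost of EUR 500 per patient. None of these four figures is in the documents.

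- Mean absence, intervention: 0.89 × 6 + 0.11 × 12 = 6.66 months
- Mean absence, control: 0.72 × 6 + 0.28 × 12 = 7.68 months
- Difference: -1.02 months × 3,000 = EUR -3,060, counted once
- With overlap at s = 0.70: -3,060 × 1.3 = EUR -3,978
- With overlap at s = 0: -3,060 × 2 = EUR -6,120

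Adding 500 and dividing by 0.17 gives about EUR -15,100, -20,500 and -33,100 per additional return to work. The apparent saving grows with the overlap.

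**Co-interventions.** With K the cost per user and d the uptake in the intervention arm minus that in the control arm, leaving them out changes the ratio by K × d / 0.17. For assumed K of EUR 1,000 to 3,000 and d from -0.20 to +0.20, the largest change is 3,000 × 0.20 / 0.17 = about EUR 3,500 in either direction. At d = 0 it is zero.

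**The case against.** The strongest reply is that the double count rests on an input the article does not fix. It says only that absence is costed from days and income. If that means income received, nothing is duplicated. Nor is anything duplicated where sick pay stays at 100%, or where baseline income, collected when patients are already sick-listed, is itself the reduced pay. An article may leave such costing detail to a fuller document. This stands as a limit on how firmly the size can be stated. It does not remove the point: the article itself fixes the components and their summation, and on the natural reading they overlap.

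Four stronger readings are tempting, and the documents do not support them.

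- A reader might infer that the whole lost-earnings item is duplicated and should be dropped. Earnings lost after sick leave ends, through fewer hours, job loss or disability, are not sick-leave days. Dropping the item would lose costs counted nowhere else.
- A reader might infer a fixed surcharge of up to 30% on every sick day. Lost earnings are a difference between two time points, not a daily accrual, so a patient back on full pay at follow-up may show none. For uninsured self-employed patients, 30% is not a ceiling either.
- A reader might infer that counting absence from the first sick day, before randomisation, biases the comparison. That absence is balanced between arms in expectation, so it adds noise and not bias.
- A reader might infer that leaving out co-interventions favours one arm. No uptake or price is given, so the direction is unknown.

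**Conclusion.** The point holds in a limited form. As defined, the sum can count part of the sick-leave loss twice, and the total does not match the societal perspective claimed for it.

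The factor of up to 2 - s assumes that absence is valued at usual income and that the pay reduction is fully captured in lost earnings. The direction, towards a larger apparent saving for the arm with more return to work, also assumes that the arms differ in absence. The euro figures above only show that the overlap need not cancel; they do not estimate the error. A reader might conclude that the cost-effectiveness ratio is simply wrong. The documents support less: it is not a valid societal ratio as defined, by an amount that cannot be computed from them.

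The primary return-to-work analysis and the sample size are unaffected.

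**What to change.** 1. Value each lost work day once, at usual income before sick leave, and say so.
2. Include in the societal total only earnings losses not already counted as absence, such as reduced hours or job loss after sick leave ends. Report the patient's income loss during sick leave separately, as a patient-perspective cost.
3. Add unit costs for the vocational and rehabilitation co-interventions recorded in the follow-up questionnaires, or narrow the stated perspective to match the costs collected.
4. Optionally, count absence from randomisation, to reduce noise.

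The cost is a change of wording in the economic analysis, a set of unit prices and slightly more costing work.
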